### Data collection

All data to be collected are part of standard clinical care. Throughout each phase of the study, the data collected will be tailored to align with the evolving focus of the research, ensuring that it remains relevant and reflects the specific objectives of each stage. At admission, we will collect data on patient demographics - including age, gestational age, sex, height and weight, comorbidities, and baseline characteristics - including reasons for intensive care unit (ICU) admission, and the start of respiratory support, presence of the pediatric acute respiratory distress syndrome (PARDS), and disease severity scores. For 4 days, beginning with the day of start of respiratory support, daily data will be collected at a time in the morning - including data on respiratory support and the respiratory status. Follow-up will be until day 28 to collect outcome data, including the date of stop of respiratory support, date of ICU discharge, and life status at ICU discharge or at day 28, whichever comes first.

Investigators will transcribe all collected data into a web-based electronic Case Report Form (eCRF) (Castor Electronic Data Capture, Amsterdam, the Netherlands).^(22)^ The eCRF complies with all applicable laws and regulations. Transcription will only take place in a secure environment. Directly identifying personal data will be separated from the research data and replaced by an assigned code. The directly identifying data will only be used to contact the patients and will only be available to the local investigators. Access to the assigned codes linked with personal data will be password-protected, restricting access to only the data directly related to the local investigator.

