### Definitions

Day 0 of invasive ventilation is defined as the day respiratory support is started in the participating ICU; in the initial phase, this is the day at which invasive ventilation is started. Day 1 is defined as the first full calendar day, with Day 2 and Day 3 representing the two consecutive mornings that follow. Pediatric acute respiratory distress syndrome is defined according to the 2023 Pediatric Acute Lung Injury Consensus Conference (PALICC-2) definition.^(23)^ Intensive care unit length of stay is defined as the time between ICU admission and discharge or death; duration of respiratory support, in the initial phase invasive ventilation, is defined as the time between initiation and successful liberation. Intensive care unit mortality is defined as any death until ICU discharge or day 28, whichever comes first.

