### Sample size calculation

The sample size will vary across each phase. In the initial phase, which focuses on invasive ventilation, the sample size calculation is based on identifying potentially modifiable factors independently associated with ICU mortality. We plan to include up to ten modifiable factors in the model to achieve this. Using logistic regression and the rule of thumb of ten events per factor, we estimated a need for one hundred events’, that is ICU deaths. Based on a conservative ICU mortality rate estimate of 3%,^(1,27)^ 3,000 patients will be required. However, depending on the actual mortality rate observed with each 4-week interval, the sample size may be adjusted accordingly. For subsequent phases, in which the study's focus and analysis plan will shift, sample sizes will be recalculated and reported in the study amendment and on Clinicaltrials.gov.

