### Statistical analysis

Descriptive statistics will be used to describe patient demographics and baseline characteristics, types of respiratory support used, device settings, and respiratory variables and parameters, including measures of oxygenation and decarboxylation. Continuous variables will be expressed in medians and interquartile ranges, and categorical variables will be expressed in frequencies and proportions. The Kruskal-Wallis test will be used to compare continuous variables, and the Chi-squared test will be used for categorical variables.

Respiratory support settings and respiratory variables and parameters at successive days will be reported in detail for the first days of respiratory care and compared between different age groups, i.e., neonates (< 1 month), infants (1 month to < 12 months), toddlers (12 months to < 3 years), preschoolers (3 years to < 6 years), school-age children (6 years to < 12 years), and adolescents (12 years to 18 years). Additionally, respiratory support settings, respiratory variables, and ventilation parameters will be compared between patients with and without PARDS and across other patient groups, including patients receiving respiratory support due to a pulmonary disease *versus* non-pulmonary conditions and patients receiving ECMO.

Key respiratory support settings, respiratory variables, and parameters will be visualized using cumulative distribution plots for the first days and line graphs over successive days. Inpatient trends over time are assessed with mixed-effect linear models with patients treated as a random effect to account for clustering and repeated measurements, and with day, different patient group and their interaction as fixed effects. P values from this analysis represent the overall difference among different patient groups over time, and p values from interaction represent the difference in trend over time among the different patient groups.

Time-to-event outcomes, like liberation from the ventilator, discharge and death, will be presented in Kaplan-Meier curves. Cox proportional hazard modelling or competing risk analyses will be used to study associations with continuous clinical outcomes, presented as hazard ratios (HR) and 95% confidence intervals (95%CIs). Logistic regression will be used to study the association between key ventilator settings and ventilation parameters and binary clinical outcomes, and will be presented as odds ratios (OR) and 95%CIs.

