## RESULTS

Of 398 patients screened, 125 were eligible for this pilot study, 91 from the UMCG and 34 from the AUMC (Figure 1S - Supplementary Material). The main reason for exclusion was not receiving invasive ventilatory ventilation. Patients were predominantly male, and most patients were neonates or infants (Table 1). The most common comorbidities were pulmonary diseases, syndromes, and genetic abnormalities. Most patients were admitted to the ICU and intubated due to pulmonary conditions, and 11% met PARDS criteria. All-cause 28-day ICU mortality was 8%, the median duration of ventilation was 4 [2 - 10] days, and the median length of ICU stay was 5 [3 - 11] days.

**Table 1 t1:** Patient demographics, baseline characteristics and outcomes

Variables		
Patient demographics		
	Age (months)	8 [2 - 72]
	Sex (male)	80 (64)
	Body weight (kg)	8 [5 - 22]
	Body height (cm)	74 [55 - 120]
	Premature birth	14 (11)
Disease severity score		
	PIM III	1 [0 - 2]
Medical history		
	Pulmonary	26 (22)
	Cardiac	23 (18)
	Neuromuscular	5 (4)
	Syndrome or genetic abnormalities	32 (26)
	Oncologic	1 (1)
	Organ transplant	8 (7)
	Chronic ventilation	2 (2)
	Mental retardation	6 (5)
Reason for ICU admission		
	Respiratory	70 (57)
	Cardiac	8 (7)
	Neuromuscular	4 (3)
	Postoperative	32 (26)
	Home ventilation	1 (2)
	Renal failure	3 (2)
	Trauma	6 (5)
	Intoxication	1 (1)
Main reason for invasive ventilation		
	Respiratory	65 (52)
	Circulatory	13 (10)
	Neurological	9 (7)
	Metabolic	1 (1)
	Postoperative weaning	33 (26)
	Trauma	4 (3)
Barotrauma during admission		
	Pneumothorax	3 (3)
	Subcutaneous emphysema	1 (1)
	Pneumomediastinum	1 (1)
Tracheostomy		3 (2)
Discharged		106 (85)
Destination of discharge		
	ICU of another hospital	5 (4)
	Ward	91 (72)
	Other healthcare facility	6 (5)
	Home	4 (3)
Duration of ventilation (days)		4 [2 - 10]
Length of ICU stay (days)		5 [3 - 11]
28-day mortality		10 (8)

PIM III - Pediatric Index of Mortality III; ICU - intensive care unit. Data presented as median with interquartile range [25^th^ - 75th quartile] or n (%).

Median time to collect all data per patient was 20 [15 - 25] minutes (Table 1S - Supplementary Material), the amount of missing data was low (Table 2S - Supplementary Material) and considered acceptable, and local investigators expressed no difficulties using Castor EDC as eCRF for data entry.

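### Kaplan-Meier curves are planned for liberation, discharge and death although these are competing events; with ordinary censoring each curve overstates the event's probability

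*Protocol article*

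**What the plan says.** Under Statistical analysis, the protocol article fixes the display of three outcomes: "Time-to-event outcomes, like liberation from the ventilator, discharge and death, will be presented in Kaplan-Meier curves". The next sentence brings in competing risks, but for association models only and as one of two options: "Cox proportional hazard modelling or competing risk analyses will be used to study associations with continuous clinical outcomes". Those results are to be reported as hazard ratios. No censoring rule is given for the curves.

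Two other sections determine how long a patient is observed. Under Definitions: "Intensive care unit mortality is defined as any death until ICU discharge or day 28, whichever comes first". Under Data collection, the outcome recorded is "life status at ICU discharge or at day 28, whichever comes first". The limitations paragraph of the Discussion confirms that follow-up is restricted to the ICU stay, with 28 days as the maximum.

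**The concern.** Kaplan-Meier assumes that a censored patient has the same future risk as those still under observation. That fails for these three outcomes. A child who dies can no longer be liberated from the ventilator or discharged alive. A child discharged alive leaves observation for ICU death, and leaves because of recovery. If such exits are censored, their probability is redistributed to the patients who remain, and one minus Kaplan-Meier no longer estimates the proportion of admitted patients who have the event. It can only err upwards.

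The competing-risk wording does not repair this, because it covers the association models and not the curves. At stake are published figures that readers would take as the share of children who died, were discharged or came off the ventilator by a given day.

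**Working it through.** **Inputs from the article**

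- Pilot size (Results): "Of 398 patients screened, 125 were eligible for this pilot study".
- Pilot deaths (Results and Table 1): "All-cause 28-day ICU mortality was 8" per cent, 10 patients.
- Pilot discharges (Table 1): 106 (85%).
- ICU stay (Results): "the median length of ICU stay was 5 [3 - 11] days".
- Planning mortality (Sample size calculation): "Based on a conservative ICU mortality rate estimate of 3" per cent.

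**Inputs assumed**

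- The timing of deaths relative to discharges is not reported, so it is varied below.
- The 125 − 10 − 106 = 9 patients with neither event are taken to be still in the ICU at day 28.

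**Step 1. Reproduce the reported proportions.** Deaths: 10/125 = 8.0%. Discharges: 106/125 = 84.8%. Remaining: 9/125 = 7.2%. With complete follow-up to day 28, Aalen-Johansen curves end at exactly 8.0% and 84.8%.

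**Step 2. One minus Kaplan-Meier when deaths and discharges share timing.** With proportional cause-specific hazards, one minus Kaplan-Meier at day 28 is 1 − S^p. Here S is the share remaining at day 28 and p is the event's share of all exits (10 + 106 = 116).

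| Outcome | Formula | 1 − KM at day 28 | Observed |
|---|---|---|---|
| ICU death, discharge censored | 1 − (9/125)^(10/116) | 20.3% | 8.0% |
| Discharge, death censored | 1 − (9/125)^(106/116) | 91.0% | 84.8% |

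The pilot gives no count of liberated patients, so no figure is offered for liberation. The direction is the same.

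**Step 3. Other models with shared timing.** A log-normal stay fitted to median 5 and quartiles 3 and 11 has log-scale SD ln(11/3)/(2 × 0.6745) = 0.963. With 8% dying and the same timing for deaths (truncated at day 28), simulation gives about 24%. A constant exit hazard with median 5 days gives about 27%. Shared timing therefore gives roughly 20% to 27%.

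**Step 4. Vary the timing of deaths.** Same log-normal stay for discharged patients, 8% deaths, deaths uniform over the window shown:

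| Deaths fall in | 1 − KM for ICU death at day 28 |
|---|---|
| Days 0–2 | about 8.5% |
| Days 0–7 | about 13% |
| Days 0–14 | about 22% |
| Days 0–28 | about 48% |

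Every scenario lies above 8%. In the earliest one the error for death is about 0.5 percentage points, while the discharge curve reaches about 96% against about 89% in that simulated population.

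**Step 5. At the planning mortality of 3%.** With 7.2% remaining at day 28 and shared timing: 1 − 0.072^(0.03/0.928) = 8.2%. If the share remaining is varied from 15% to 3%, the result runs from 6.5% to 10.3%.

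**The case against.** The strongest reply is that no censoring rule is written. The Statistical analysis section says death, not ICU death, and Study endpoints also lists mortality in hospital and at day 28. If discharged patients were kept at risk to day 28, the curve for ICU death would end at 8.0%. Likewise, patients who die could be kept at risk as never liberated, in line with the zero ventilator-free days assigned to them under Calculations. This stands as a possibility. It is not what an unqualified Kaplan-Meier analysis does, however, and follow-up that ends at ICU discharge makes censoring there the natural reading.

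A second reply is that the curves only present outcomes. This also stands. The sample size rests on logistic regression of ICU mortality, and mortality is analysed by relative risk, LOWESS and adjusted logistic regression. None of these uses the curves, and the crude proportion would presumably be reported beside them, as in the pilot.

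Several stronger readings are tempting but not supported:

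- **A single narrow figure for apparent mortality.** The article does not report death timing, so only a range can be given.
- **Death is always the worst affected.** With early deaths, the discharge curve has the larger absolute error.
- **Comparisons by age, PARDS or region will be distorted.** The comparisons set out by age and PARDS concern respiratory support settings, variables and parameters. Nowhere are Kaplan-Meier curves specified by subgroup.
- **The Cox option is wrong.** A Cox model that censors competing events is a valid cause-specific hazard model.

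**Conclusion.** The point holds for the descriptive curves and should be fixed. The article states a method that, with ordinary censoring, overstates the probability of liberation, discharge and death.

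On the pilot counts and shared timing, ICU death would appear as about 20% rather than 8%, and discharge as about 91% rather than 85%. The direction is certain once competing exits are censored. The size is not: it depends on unreported death timing, with about 8.5% to 48% spanning the scenarios tried for ICU death. The pilot figures also assume that the 9 unaccounted patients were still in the ICU at day 28.

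A reader might infer that the mortality results as a whole are compromised. They are not, because the logistic regression of ICU mortality stands apart from the curves. Calling the outcomes continuous while reporting hazard ratios is a slip of wording without analytic consequence.

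**What to change.** In Statistical analysis, replace the Kaplan-Meier curves with Aalen-Johansen cumulative incidence curves. Name the competing event for each: death for liberation and for discharge, and discharge alive for ICU death. State that patients without an event are censored at day 28.

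In the association sentence, change continuous to time-to-event. Cause-specific Cox models are acceptable there; adding a Fine-Gray model is optional.

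The cost is a few words in the plan and a different R function. No new data are needed, since the dates and vital status at ICU discharge or day 28 are already collected.

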A robust locally weighted scatter plot smoothing (LOWESS) method will be used to investigate the association between ICU mortality and key ventilatory variables and parameters, including V^T^, Ppeak, PEEP, FiO^2^, RR, PaO^2^/FiO^2^, ΔP, MP and ME. The smoothing curves will be generated with a bandwidth of 0.66, a polynomial regression with 1 degree of freedom, and a tricubic weighting function so that observations furthest from the point of interest are assigned the least weight.

In a univariate analysis, the impact of the single key ventilatory variables on mortality will be assessed by estimating the relative risk of all-cause 28-day ICU mortality. Multivariate logistic regression will be used for the adjusted analysis, adjusting for unequal distribution of effect modifiers. We will adjust for baseline covariates selected according to clinical relevance, including age, sex, weight, comorbidities, and severity of illness. Results will be shown as ORs with 95%CI. Multiple imputation will be performed to account for missing values.

Data will be analyzed with R version 4.2.2 (R Core Team, 2022, Vienna, Austria). Statistical uncertainty will be expressed by 95%CIs. A p value < 0.05 is considered statistically significant.

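### Read literally, the planned robust LOWESS of ICU mortality discards the deaths and draws curves at zero; drop 'robust' and state zero robustness iterations

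*Protocol article*

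**What the plan says.** All of the relevant text is in the Protocol article.

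- **Method** (Statistical analysis): "A robust locally weighted scatter plot smoothing (LOWESS) method will be used to investigate the association between ICU mortality" and a list of nine variables: tidal volume, peak pressure, PEEP, FiO2, respiratory rate, PaO2/FiO2, driving pressure, mechanical power and mechanical energy.
- **Settings** (same section): "The smoothing curves will be generated with a bandwidth of 0.66, a polynomial regression with 1 degree of freedom, and a tricubic weighting function". The stated purpose of the weights is that distant observations count least. No number of robustness iterations is given, and nothing says that residual reweighting is switched off.
- **Software** (same section): "Data will be analyzed with R version 4.2.2". No function is named.
- **Outcome** (Definitions): "Intensive care unit mortality is defined as any death until ICU discharge or day 28, whichever comes first". Each patient therefore contributes a 0 or a 1.
- **Expected rate**: 3% ICU mortality in Sample size calculation, and 8% (10 of 125) in the pilot reported under RESULTS.

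**The concern.** Robustness iterations protect a smooth of a continuous outcome against a few wild values. They do so by reducing or removing the weight of points that lie far from the first fit.

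With a rare binary outcome, the points far from the fit are the events. Survivors lie just below the curve and deaths lie almost a full unit above it. A rule that treats large residuals as outliers therefore deletes the information the curve is meant to display.

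Among the methods the article describes, this smooth is the one that shows the shape of each mortality association. If it is run as worded, a flat line at zero appears whether the true association is absent, linear or curved.

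**Working it through.** The plan gives no numerical result for this analysis, so there is no figure of its own to reproduce. The check runs the stated method at the plan's own mortality rates.

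**Inputs from the article.** Span 0.66, local linear fit, tricube distance weights, binary outcome, mortality 3% (planning) and 8% (pilot), 3,000 planned patients (3,000 × 0.03 = 90 deaths).

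**Input from the standard method.** After the first fit, with residuals e and s = median |e|, the robust version multiplies each weight by (1 − (e/6s)²)² if |e| < 6s, and by 0 otherwise. It then refits. R's `lowess()` does this three times unless told not to.

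**Step 1: flat risk p.** The first fit is about p. Survivors have |e| ≈ p and deaths have |e| ≈ 1 − p. Survivors are the large majority, so s ≈ p and the cutoff is 6p.

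| Mortality p | Cutoff 6p | Residual of a death, 1 − p | Weight of deaths |
|---|---|---|---|
| 3% | 0.18 | 0.97 | 0 |
| 8% | 0.48 | 0.92 | 0 |

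All deaths are removed when 1 − p > 6p, that is p < 1/7 = 14.3%. Only zeros remain, so the refit is zero.

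**Step 2: a moderate association.** Simulation with n = 3,000 and a log-odds slope of 0.08 per cmH2O of driving pressure. The slope is an assumption. Entries are fitted risks at 10/16/22 cmH2O.

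| Mortality | True risk | Robust fit | No robustness iterations |
|---|---|---|---|
| 3% | 1.8/2.9/4.6% | 0/0/0% | 1.1/2.5/5.2% |
| 8% | 4.9/7.7/11.9% | 0/0/0% | 4.4/8.5/11.2% |

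One robustness iteration was enough to give zero in these settings. In a separate simulated data set at 3%, R's `lowess(f = 0.66)` at its defaults also gave 0/0/0%, and with `iter = 0` it gave 1.4/3.1/6.1%.

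**Step 3: other slopes and predictor shapes.** A separate implementation used odds ratios of 1 to 3 per SD and normal, integer PEEP-like, skewed FiO2-like and tidal-volume-like predictors.

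- *At 3%*: no death kept any weight after the first pass, and every curve was exactly zero. With normal predictors the cutoff was about 0.11 to 0.21, while the smallest residual of any death was 0.64 to 0.96.
- *At 8%*: the curve was zero in nearly all runs. The exceptions had odds ratios of 2.5 to 3 per SD, where about 1 to 5% of deaths, in the extreme tail, kept weight. With the PEEP-like predictor at odds ratio 2.5 (n = 1,250), three of five runs showed a tail upturn, with maxima of 0.72, 0.06 and 0.55. The rest of the curve stayed at zero.
- *Above 14%*: the limit in Step 1 concerns the first pass only. At 15% and 20% with a flat risk, all deaths survived that pass, yet three iterations still ended at zero.

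**Step 4: R's other smoother.** `loess(span = 0.66, degree = 1)` with its default gaussian family does no residual reweighting. In runs with the same slope it gave 1.3/2.9/5.5% at 3% mortality (true 1.8/2.9/4.5%) and 4.3/8.5/11.0% at 8% (true 4.9/7.7/11.9%). In a separate run at 3%, its robust option (`family = 'symmetric'`) stopped with a numerical error.

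**The case against.** The strongest reply is that the article does not clearly commit to residual reweighting. Everything it spells out (span, degree, tricube weights and their purpose) describes distance weighting, and the problem hangs on one adjective. A stated polynomial degree fits R's `loess()` at least as well as `lowess()`, which has no degree argument, and Step 4 shows that `loess()` at its defaults works. The authors may well intend a non-robust smooth.

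That stands as a limit on the claim but does not remove it. Tricube distance weights belong to every LOWESS and do not make it robust, so the word either calls for the failing procedure or is wrong. This is a stated choice of method, and not a detail left to an analysis plan.

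The reply is also right on consequence. The curves carry no test, estimate or decision rule. Nine curves lying on zero would be noticed at first plotting. The cost would then be a change of method after the outcome data had been seen.

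A reader might go further and infer that every death is lost for every variable whatever the truth, or that the study's mortality findings are compromised. The documents do not support either. At 8% with very steep associations some tail deaths keep weight. The odds ratios, the relative risks and the sample size do not depend on the smooth.

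**Conclusion.** The point holds for the wording as it stands. Under the ordinary meaning of robust LOWESS, the planned curves are exactly zero at the planning rate of 3%. At the pilot's 8% they are zero apart from possible tail upturns when associations are very steep. They would carry no usable information on the shape of the associations.

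This rests on 'robust' meaning bisquare reweighting with the cutoff at 6 times the median absolute residual, on at least one such iteration being run, and on the simulated slopes and predictor shapes. If the authors mean a non-robust smooth, the method is sound and only the word needs correcting.

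Severity is moderate: a descriptive display fails, while the inferential analyses are untouched.

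**What to change.** In Statistical analysis, delete 'robust' and add that no robustness iterations are used, leaving span 0.66, local linear fit and tricube distance weights as they are. In R this is `lowess(..., iter = 0)` or `loess(..., family = 'gaussian')`. Naming the function would remove the remaining ambiguity.

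An optional alternative is a logistic model with restricted cubic splines and 95% bands. It keeps fitted risks between 0 and 1, whereas the non-robust linear smooth dipped slightly below zero in some simulations (to −0.026 at 8% mortality with an odds ratio of 3 per SD). It can also adjust for age and severity. This is a refinement, since the non-robust smooth already recovers the shape.

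The cost is one word and one function argument, or a few lines of code for the spline. Data collection, sample size and the other models do not change.

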The most used ventilation mode was PCV (92%) (Table 2). Most patients received V_T_ of less than 8mL/kg, with younger children receiving lower median V_T_ than older patients (Figure 2). Younger patients received lower median PEEP than older patients. Median FiO_2_ and median RR were higher, and median ΔP was lower in younger children. PARDS patients received lower V_T_, higher median PEEP and FiO_2_, and lower median ΔP than non-PARDS patients.

**Table 2 t2:** Ventilator settings, ventilation variables and parameters, and arterial blood gas analysis at day 0

		All n = 125	Neonates n = 10	Infants n = 61	Toddlers n = 14	Preschoolers n = 8	School-aged n = 16	Adolescents n = 16
Ventilation mode								
	Volume controlled ventilation	9 (7)	0 (0)	0 (0)	0 (0)	1 (13)	5 (31)	3 (19)
	Pressure controlled ventilation	115 (92)	10 (100)	60 (98)	14 (100)	7 (88)	11 (68)	13 (81)
	Volume support	1 (1)	0 (0)	1 (2)	0 (0)	0 (0)	0 (0)	0 (0)
Ventilator settings								
	V_T_ (mL/kg ABW)	6 [5 - 7]	6 [5 - 6]	6 [5 - 7]	7 [4 - 8]	9 [7 - 9]	7 [6 - 8]	6 [5 - 7]
	PEEP (cmH_2_O)	6 [5 - 8]	7 [5 - 8]	6 [5 - 8]	7 [6 - 8]	7 [6 - 8]	6 [5 - 8]	7 [5 - 9]
	RR (breath/min)	30 [25 - 36]	36 [35 - 38]	35 [30 - 40]	29 [26 - 33]	26 [22 - 30]	20 [20 - 25]	19 [15 - 24]
	FiO_2_ (%)	40 [30 - 50]	45 [36 - 58]	40 [30 - 50]	40 [40 - 45]	38 [29 - 45]	30 [30 - 40]	45 [39 - 63]
Ventilation variables and parameters								
	Ppeak (cmH_2_O)	23 [20 - 27]	23 [20 - 26]	24 [21 - 27]	26 [22 - 30]	24 [18 - 26]	20 [17 - 26]	21 [19 - 28]
	Pmean (cmH_2_O)	12 [10 - 14]	10 [10 - 13]	12 [11 - 14]	13 [11 - 16]	13 [10 - 15]	10 [9 - 13]	11 [8 - 13]
	etCO_2_ (kPa)	6 [5 - 7]	5 [3 - 6]	6 [6 - 7]	6 [5 - 7]	5 [5 - 5]	5 [4 - 6]	5 [5 - 6]
	C_RS_	3 [2 - 7]	1 [1 - 2]	2 [1 - 3]	4 [3 - 5]	6 [5 - 10]	15 [11 - 18]	23 [20 - 26]
	ΔP (cmH_2_O)	16 [14 - 19]	17 [12 - 18]	17 [15 - 19]	18 [15 - 22]	17 [13 - 21]	13 [10 - 18]	14 [10 - 19]
	MP (J/minute)	2 [1 - 5]	1 [1 - 1]	2 [1 - 2]	3 [3 - 5]	5 [3 - 5]	5 [4 - 8]	8 [6 - 10]
	ME (mJ/kg)	9 [7 - 11]	10 [6 - 10]	8 [7 - 10]	11 [7 - 14]	11 [10 - 14]	10 [8 - 12]	9 [7 - 10]
Arterial/capillary blood gas analysis								
	pHa	7.4 [7.3 - 7.4]	7.4 [7.3 - 7.4]	7.3 [7.3 - 7.4]	7.3 [7.3 - 7.4]	7.4 [7.3 - 7.4]	7.4 [7.3 - 7.4]	7.4 [7.4 - 7.4]
	PaO_2_ (kPa)	6.7 [6.3 - 6.7]	5.2 [5.2 - 5.3]	6.7 [6.0 - 6.7]	6.7 [6.7 - 6.7]	6.7 [6.7 - 6.7]	6.7 [6.7 - 6.8]	6.7 [6.7 - 6.7]
	PaCO_2_ (kPa)	5.8 [5.2 - 6.6]	5.8 [5.4 - 6.3]	6.6 [5.6 - 6.7]	6.1 [5.8 - 6.3]	4.5 [4.2 - 5.2]	5.1 [4.7 - 5.7]	5.2 [5.0 - 5.7]

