The proposed study offers several strengths. PRoVENT-PED's adaptive design allows for a flexible focus on evolving clinical priorities, enabling the investigation of key topics such as invasive and noninvasive ventilation, weaning, patient-ventilator asynchronies, and extracorporeal support. Once the required sample size for one topic is reached, the study can seamlessly transition to the next, ensuring responsiveness to emerging challenges in pediatric intensive care. Its prospective design ensures more accurate data collection on exposures, confounders, and outcomes compared to retrospective studies, reducing the risk of bias and improving the reliability of the findings. The planned large sample size is expected to provide robust insights into associations between ventilation practice and clinical outcomes. By including diverse ICUs across resource-limited and resource-rich settings worldwide, the study captures variations in practice, patient populations and ventilation strategies, enabling exploration of geo-economic differences and their impact on outcome. Additionally, data collection across different seasons and patient groups will allow for comprehensive subgroup analyses, including patients with and without PARDS, various age categories, and diverse disease conditions.

A pilot study was conducted to test the feasibility of data collection and assess the presence of missing data. Most data were effectively captured. Notably, the absence of specific data does not necessarily indicate missingness but may reflect clinical practice. For instance, blood gas analyses might not have been performed if not clinically indicated, and such cases were not classified as missing data. In contrast, variables like patient height, which should have been recorded but were not, were treated as genuinely missing. This distinction was carefully accounted for in the analysis. Furthermore, the time required for data collection was considered sufficiently low, even when accounting for settings such as low- and middle-income countries (LMICs), where the time available for such tasks may be more limited.

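### The LOWESS mortality curves for RR and MP pool all ages with no stated age handling, so if mortality differs by age they partly show age; an age-ranked curve should sit beside each.

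*Protocol article*

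**What the plan says.** All of this is in the protocol article; section names are given for each point.

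- **The curves (Statistical analysis).** "A robust locally weighted scatter plot smoothing (LOWESS) method will be used to investigate the association between ICU mortality and key ventilatory variables and parameters". The same sentence names the nine variables, RR and MP among them; the curves concern the "association between ICU mortality and key ventilatory variables and parameters, including V^T^, Ppeak, PEEP, FiO^2^, RR, PaO^2^/FiO^2^, ΔP, MP and ME".
- **Their specification (same paragraph).** "The smoothing curves will be generated with a bandwidth of 0.66, a polynomial regression with 1 degree of freedom, and a tricubic weighting function". No age stratum, adjustment or scaling is given for the curves.
- **The adjusted model (next paragraph).** For the multivariable logistic regression: "We will adjust for baseline covariates selected according to clinical relevance, including age, sex, weight, comorbidities, and severity of illness". Age is therefore handled in the adjusted odds ratios.
- **Age groups (Statistical analysis).** Six are defined. Settings and parameters will be "compared between different age groups, i.e., neonates (< 1 month), infants (1 month to < 12 months" and so on up to adolescents. The mortality curves are not mentioned there.
- **Subgroups (Discussion).** The article foresees "comprehensive subgroup analyses, including patients with and without PARDS, various age categories, and diverse disease conditions", in general terms and not tied to the curves.
- **Scaling (Calculations).** Tidal volume (V_T) and mechanical energy (ME) are expressed per kg. MP (Equations 6 and 7) multiplies unscaled V_T by RR.

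**The concern.** RR and MP change with age for physiological reasons. A newborn breathes fast with tiny volumes; an adolescent breathes slowly with large ones. On a pooled raw axis, one end of the RR curve is mostly infants and the other mostly older children. MP runs the opposite way.

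If infants and older children die at different rates, each curve slopes even when neither variable affects death within any age group. Higher mortality in infancy would make high RR look harmful and high MP look protective; lower mortality in infancy would reverse both. The curves are there to investigate an association with ICU mortality, and the article names no age-adjusted display of its shape. What is at stake is how two of the nine curves are read.

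**Working it through.** **The plan's own figure.** The article gives no number for these curves. The nearest is the sample size: 10 factors x 10 events = 100 ICU deaths, put at 3,000 patients. At 3% mortality, 3,000 patients give 90 deaths, and 100 deaths need 100/0.03 = 3,334. That gap is a separate matter. Here it only shows that the curves rest on about 90-100 deaths.

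**Step 1: how far RR and MP depend on age.** Inputs are the Table 2 medians [quartiles], neonates to adolescents, with n = 10, 61, 14, 8, 16, 16:

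- RR (breaths/min): 36 [35-38], 35 [30-40], 29 [26-33], 26 [22-30], 20 [20-25], 19 [15-24]
- MP (J/min): 1 [1-1], 2 [1-2], 3 [3-5], 5 [3-5], 5 [4-8], 8 [6-10]

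Share between age groups = B/(B + W). B is the n-weighted variance of the medians. W is the n-weighted mean of (IQR/1.349)².

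- RR: weighted mean 3,733/125 = 29.86; B = 117,043/125 - 29.864² = 44.49; W = (9,084/125)/1.349² = 39.93; share = 44.49/84.42 = **53%** (49-56% allowing for rounding in the table).
- MP: weighted mean 422/125 = 3.376; B = 2,004/125 - 3.376² = 4.63; W = (661/125)/1.349² = 2.91; share = 4.63/7.54 = **61%** (52-69% allowing for rounding). Log-normal draws with slightly widened quartiles give 50%.
- Other listed variables in Table 2: V_T/kg 18%, ME 14%, ΔP 11%, Ppeak 10%, FiO2 9%, PEEP 5%.

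Only RR and MP stand out.

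**Step 2: what the raw curve shows when nothing is going on.** Mortality by age is not in the documents, so it is assumed. The simulation has 3,000 children with the pilot age mix, values normal within age group (neonatal MP SD set to 0.2 because the printed quartiles are 1-1), overall mortality 3%, and risk depending on age group only. LOWESS is local linear with bandwidth 0.66 and tricube weights, **without robustness iterations**, fitted to expected risk.

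For a ratio of 2 (under 12 months versus 6 years and over, with √2 in between), the risk at 6 years and over is 0.03/(0.568 x 2 + 0.176 x 1.414 + 0.256) = 1.83%. It is 2.59% at 1 to <6 years and 3.66% under 12 months. The true within-age relation is flat, but the expected curve is:

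| Percentile | 10 | 25 | 50 | 75 | 90 |
|---|---|---|---|---|---|
| RR curve, % | 2.1 | 2.5 | 3.2 | 3.5 | 3.6 |
| MP curve, % | 3.5 | 3.5 | 3.4 | 2.5 | 2.0 |

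Ratio of the curve at the 90th to the 10th percentile, by assumed age pattern:

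| Mortality pattern | RR | MP |
|---|---|---|
| Young:old 0.5 | 0.56 | 1.72 |
| Young:old 1 | 1.00 | 1.00 |
| Young:old 1.5 | 1.37 | 0.72 |
| Young:old 2 | 1.71 | 0.58 |
| Young:old 3 | 2.25 | 0.42 |
| U-shaped (under 12 months and 6 years and over both 2-fold) | 1.05 | 0.94 |
| Neonates only 2-fold | 1.13 | 0.77 |

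A separate simulation, contrasting under 12 months with all older children, gives 1.80 (RR) and 0.57 (MP) at a ratio of 2.

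**Step 3: sampling noise.** With 0/1 deaths at 3.33% (about 100 deaths) and an age ratio of 2, the 5th-95th percentile range of the curve ratio is 1.13-2.79 for RR and 0.33-0.91 for MP.

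**Step 4: which remedy holds.**

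- An age-group z-score curve is flat at 3.0% only if every age group has the same distributional shape. With split-normal draws matched to the Table 2 quartiles and an age ratio of 2, the MP z-score curve is 3.28, 2.95, 3.03, 3.09, 2.62%. Its end-to-end ratio is 2.62/3.28 = 0.80.
- Percentile rank within age group has the same distribution in every group, so it cannot carry age. That curve stayed at 3.0% in every pattern tried, skewed draws included.
- With 1 or 3 robustness iterations on 0/1 deaths at about 3%, the fitted curve falls to 0% throughout. Deaths are so rare that the reweighting treats them as outliers.

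**The case against.** The strongest case against has four parts.

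1. **Age is handled where inference is made.** The logistic model adjusts for age and weight, and the sample size is tied to logistic regression. This stands, and it limits the point. A reader might infer that age confounds the whole mortality analysis; the documents do not support that. Nor is the crude univariate relative risk at fault. But an adjusted odds ratio does not correct how the RR and MP curves look.

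2. **No bias is demonstrated.** There is no mortality by age: the pilot reports 10 deaths in 125 without a split, and five of its six age groups have 8 to 16 children. This stands. A reader might infer that the curves will mislead, or in which direction; neither is established.

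3. **The article does not rule out age-stratified curves, and a fuller plan may contain them.** That is fair, and nothing is contradicted. However, the article fixes these curves down to the weighting function and defines age groups for other analyses, so age is a natural element to fix with them.

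4. **The article says robust LOWESS, and the figures here use none of the usual robustness iterations.** This stands. If the word means those iterations, the raw curve would be 0% and so would any added curve. The figures describe the curves only with the iterations off, so the remedy has to say so.

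**Conclusion.** The point holds in a narrow, conditional form. As specified, the RR and MP curves pool all ages on axes where age group explains 53% (RR) and about 50-61% (MP) of the variance in the pilot. If mortality is 2-fold higher under 12 months than at 6 years and over, a false 90th-to-10th percentile ratio of about 1.7 (RR) and 0.6 (MP) follows with no ventilation effect. With equal mortality there is none, and with the U-shaped pattern little.

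This rests on rounded pilot values from 125 children, an assumed mortality pattern, and LOWESS without robustness iterations. It does not extend to the other listed variables that Table 2 reports, which depend far less on age, or to the adjusted odds ratios. It is an inexpensive improvement to a secondary, graphical analysis; confidence is medium.

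**What to change.** In the LOWESS paragraph of Statistical analysis, for RR and MP only:

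- Keep the raw curve and label it as unadjusted for age.
- Beside it, add a LOWESS curve of ICU mortality against the child's percentile rank of RR or MP within the six age groups already defined. Rank is preferred to a z-score because of the residual MP gradient shown above.
- State that the curves are fitted without robustness iterations, because the outcome is binary at about 3%.
- Show 95% confidence bands, since about 100 deaths leave the curve noisy.
- Base any reading of the shape of the relation on the age-ranked curve.

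The cost is one derived variable and one extra panel for each of two variables, from data already collected. The downside is that the rank axis is not in bedside units and depends on the study sample, which is why the raw curve stays.
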